## Reporting of Adverse Events

1. The investigator informed the subjects or their legally acceptable representatives of all potential AEs that may occur after IP administration and instructed them to report any symptoms that appear after administration.
2. For any systemic or clinicopathologic symptoms occurring after IP administration, the type, duration (start date and end date), severity, treatment, drugs administered, course, and causal relationship to the IP will be recorded and retained in the eCRF in accordance with the Good Clinical Practice.
3. In the event of an AE, the investigator should immediately provide necessary tests and treatment. In the event of a SADR, appropriate and prompt measures should be taken in accordance with Section 8.4.
4. Additional safety information should be periodically reported until the end of the ADR (resolution of the ADR, lost to follow-up, etc.).

## Reporting of Serious Adverse Events

1. Reporting method of serious adverse events

All serious adverse events (SAEs) that occur during the clinical study must be reported to the sponsor (Daewoong Pharmaceutical Co., Ltd.) within 24 hours of the investigator becoming aware of them, regardless of their causal relationship with the investigational product. The report should be sent to the following contact (Email).

- E-mail: [contact]

The initial report should include the following:

- Protocol Number
- Subject Information
- Name of the AE (symptoms, signs or diagnosis)
- Start and End Dates of the AE
- Severity of the AE
- Causality with the Investigational Medicinal Product
- Reporter Information

The investigator should make a follow-up report when additional information about an SAE becomes available. The investigator should periodically report until the end of the SAE (resolution, lost to follow-up, etc.).

1. Actions for Serious Adverse Events

The principal investigator and the sub-investigator should ensure the safety of subjects and minimize AEs by taking an appropriate measure quickly in the event of any SAEs. If an “SAE” occurs during the study, the responsibilities of each responsible person are as follows.

- Principal Investigator: The principal investigator must promptly contact the sponsor and/or the Contract Research Organization (CRO) within 24 hours of becoming aware of any serious adverse events (SAEs) that occur during the study. All initial SAE reports must be documented using the “Serious Adverse Event Report Form.” The principal investigator must also report to the Institutional Review Board (IRB) within the time frame specified by the IRB When reporting death cases, the principal investigator should submit additional information such as autopsy reports (only if an autopsy is performed) and terminal medical reports to the Sponsor and the IRB.
- Sub-Investigator: The sub-investigator must immediately report any SAEs that occur during the study to the principal investigator, sponsor, and/or CRO and follow up with a detailed report.
- IRB: The IRB shall instruct the principal investigator to take necessary actions if serious adverse drug reactions or new information that could negatively impact the safety of the subjects or the conduct of the study arises.

## Pregnancy

Administration of this investigational product (IP) in pregnant women is restricted or requires precautions, and pregnancy is contraindicated in principle. However, if pregnancy is inevitably confirmed, the following guidelines should be complied with:

1. Pregnancy itself will not be considered as an AE during the study. Additionally, elective abortions (excluding therapeutic abortion) without any complications or hospitalization for normal delivery of a healthy newborn will not be considered as an AE.
2. If a female subject or sexual partner (or spouse) of a male subject becomes pregnant during the study, a “Pregnancy report” should be prepared and submitted to the sponsor and/or CRO within 24 hours of becoming aware of the pregnancy, via E-mail. The investigator should make follow-up reports of all pregnancies until 7 days from delivery or conclusion of the pregnancy.
3. Serious maternal complications, spontaneous abortion, ectopic pregnancy, stillbirth, neonatal death, congenital anomaly, etc. will be considered as an SAE and reported to the sponsor by the investigator accordingly.

# Data Management

## Source Documents

Source documents are defined as records and materials resulting from data collection activities and observations in this study. They include, but are not limited to, the following clinical study-related materials.

1. Source document data and records: Subject information sheets and consent forms, medical records, laboratory test records, records held by the pharmacy and laboratory departments involved in the clinical study, etc.
2. All original records or certified copies of original records containing clinical findings, observations, or other activities necessary for the replication or evaluation of the clinical study.

All source documents in this study will be recorded and stored by the investigators at the study site. Access to source documents will be restricted to authorized personnel only.

## Data Entry

The sponsor or delegated personnel will manage the data according to the Standard Operating Procedures (SOP). Monitors will ensure that the entries in the eCRF match the source documents and that the information is appropriate. They will take measures to prevent further collection or additional modifications of the eCRF. Data managers will check the appropriateness of the data entered in the eCRF and verify that it is correctly entered into the database, checking for any logical inconsistencies in the database.

Data for this study will be collected using a pre-designed eCRF. All Electronic Data Capture (EDC) systems used will comply with the Code of Federal Regulations (CFR) (21 CFR Part 11) and guidelines for processing and managing electronic data in clinical studies. The EDC system is an accredited electronic data collection system accessible only by authorized personnel. The system will record all traceable activities, including eCRF data entry, modification, storage, and deletion. The sponsor may request verification or correction of the collected data during the processing. The investigator is responsible for responding to these requests by rechecking or correcting the data and ensuring the data entered into the eCRF is accurate, complete, decipherable, and timely through electronic signatures. After the study concludes, copies of the eCRFs created through the EDC system will be stored on electronic media and provided to each study site. They will be archived under the same conditions as other essential documents.

## Data Verification

In case of discrepancies between the eCRF and source documents, inappropriate entries, or logical inconsistencies, the sponsor or data manager, along with the principal investigator, will review the validity of the concerned items. If necessary, corrections will be made and documented accordingly.

Once the sponsor verifies that there are no errors in the eCRF and the database, the database will be locked to prevent any unauthorized or accidental changes (database lock). Once locked, the clinical study data cannot be modified arbitrarily.

## Data Storage

The principal investigator is responsible for storing and managing all collected data and records (including electronic documents) at each site, including those from subjects who withdrew consent or dropped out.

All documents collected during the study must be stored in a secure, locked cabinet accessible only to the principal investigator, co-investigators, and delegated sub-investigator.

According to Article 15 of the Enforcement Rules of the Bioethics and Safety Act, the principal investigator must retain all documents for three years from the end date of the clinical study (However, the sponsor may extend the storage period if deemed necessary).

These documents are subject to audits by the sponsor or relevant regulatory authorities, and the investigator must not destroy any documents related to the clinical study without the sponsor's written consent. The investigator must seek preventive measures to avoid any accident or early destruction of such documents.

Upon the expiration of the retention period, paper documents will be shredded immediately, and electronic documents will be destroyed in a manner that prevents their recovery or restoration, as per the sponsor's agreement.

## Access to Data

Sponsor, monitor and auditor involved in this study may have access to the subject’s records for the purpose of monitoring and auditing the study and managing the progress. By entering into the study agreement, the investigator acknowledges that monitors and auditors from the sponsor and/or Contract Research Organization (CRO) may review the study subjects' charts and case report forms.

This information must be kept confidential and facilities with appropriate confidentiality standards and management protocols must be in place. The investigator must provide the necessary support to the sponsor and/or CRO. The investigator must also grant authorized representatives from the sponsor, regulatory authorities, and IRB direct access to the original medical records of the study subjects for the verification of study procedures and data.

# Evaluation Criteria and Methods, and Statistical Analysis Methods

## Endpoints

1. **Efficacy Endpoints**
2. **Primary Efficacy Endpoint**

- Change in BMI and weight at 24 weeks compared to baseline

1. **Secondary Efficacy Endpoints**
2. Change in BMI and weight at 12 weeks compared to baseline
3. Proportion of subjects achieving ≥ 5% reduction in BMI and weight at 12 and 24 weeks compared to baseline
4. Change in body composition analyzer indicators (body fat mass, visceral fat mass, muscle mass, waist/hip circumference, etc.) at 12 and 24 weeks compared to baseline
5. Change in HbA1c at 12 and 24 weeks compared to baseline
6. Change in FPG at 12 and 24 weeks compared to baseline
7. Proportion of subjects achieving HbA1c < 7% at 12 and 24 weeks compared to baseline
8. Proportion of subjects achieving HbA1c < 6.5% at 12 and 24 weeks compared to baseline
9. Proportion of subjects achieving therapeutic response [change in HbA1c (baseline HbA1c – HbA1c at each evaluation time point) > 0.5% or HbA1c < 7%] at 12 and 24 weeks compared to baseline
10. **Exploratory Endpoints**
11. Change in lipid levels (total cholesterol, LDL-C, HDL-C, triglycerides) at 12 and 24 weeks compared to baseline
12. Change in liver function markers (AST, ALT, γ-GTP) at 12 and 24 weeks compared to baseline
13. Change in renal function markers (e-CFR, UACR (Urine Albumin to Creatinine Ratio), UGCR (Urine Glucose to Creatinine Ratio)) at 12 and 24 weeks compared to baseline
14. Change in other body composition analyzer indicators (body water, intracellular water, extracellular water, extracellular water ratio, abdominal fat percentage, etc.) at 12 and 24 weeks compared to baseline
15. **Safety Endpoints**
16. Definition of an adverse drug reaction (ADR)
17. Incidence rate and number of occurrences of Serious ADRs (SADRs)
18. Adverse events of Special Interest^*^

* Hypoglycemia, urinary tract infection, genital infection, frequent urination, polyuria

1. Laboratory tests, vital signs, physical examination results

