## Inclusion Criteria

Select individuals who meet all of the following criteria:

1. 1) Adults aged 19 to 80 years, both male ∙and female
2. 2) Patients with Type 2 Diabetes who, based on medical judgment by the investigator (responsible physician) and according to the approved indications, are about to receive Envlo Tab. or Envlomet SR Tab. for the first time

- Enavogliflozin monotherapy

- Enavogliflozin combination therapy with two agents (in combination with metformin)

- Enavogliflozin combination therapy with three agents (in combination with metformin and a DPP4 inhibitor)

1. 3) Patients with pre-obesity or higher stages according to the 2022 Obesity Treatment Guidelines of the Korean Endocrine Society*

* Obesity Treatment Guidelines of the Korean Endocrine Society

- Pre-obesity: BMI 23-24.9 kg/m^2^

- Stage 1 obesity: BMI 25-29.9 kg/m^2^

- Stage 2 obesity: BMI 30-34.9 kg/m^2^

- Stage 3 obesity: BMI >35 kg/m^2^

4) Individuals who plan to engage in appropriate exercise and dietary therapy for blood glucose control during the observational study period

5) Women of childbearing potential and men who agree to use appropriate contraceptive methods* or have no plans for pregnancy during the observational study period

*Hormonal contraceptives, intrauterine device (IUD) or intrauterine system (IUS) implants, vasectomy, tubal ligation, double barrier methods (simultaneous use of cervical cap or diaphragm with male condom), etc.

6) Individuals who have listened to and understood the detailed explanation of the observational study and the characteristics of the investigational products, and have voluntarily signed a written informed consent agreeing to participate in the study and to comply with subject precautions during the study period

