## Exclusion Criteria

Individuals who meet any of the following exclusion criteria will be excluded from this observational study:

1) Individuals with diabetes other than Type 2 Diabetes (e.g., Type 1 Diabetes, Diabetic Ketoacidosis, Gestational Diabetes, etc.)

2) Individuals who fall under the contraindications for administration according to the approved conditions of Envlo Tab./Envlomet SR Tab.

- Patients with hypersensitivity or a history of hypersensitivity to any component of Envlo Tab. or Envlomet SR Tab.

- Patients with an eGFR less than 30 mL/min/1.73 m²

- Patients with renal impairment with an eGFR less than 60 mL/min/1.73 m², end-stage renal disease, or those on dialysis

- Individuals with moderate to severe hepatic impairment (AST or ALT > 3 times the upper limit of normal, Total Bilirubin > 2 times the upper limit of normal, hepatitis, or liver failure)

- Individuals classified as class III or IV according to the New York Heart Association (NYHA) classification

3) Individuals who have undergone treatment with obesity medications or weight loss drugs, or other treatments (surgery, diet, etc.) leading to unstable weight within 3 months prior to the enrollment date

4) Individuals with mental incapacity

5) Pregnant or breast-feeding women

6) Individuals participating in another clinical study and receiving (applying) investigational drugs or investigational medical devices

7) Individuals deemed unsuitable for participation in this observational study based on the judgment of the investigator (responsible physician)

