# Method of Observational Study

## Overall Design of Observational Study

This observational study is designed as a prospective, multicenter observational study to confirm the weight loss efficacy and safety of Envlo Tab. or Envlomet SR Tab. over 24 weeks in patients with Type 2 Diabetes in real-world primary care settings.

The study plans to recruit patients with Type 2 Diabetes who are scheduled to receive Envlo Tab. or Envlomet SR Tab. based on the medical judgment of the investigator (responsible physician) and in accordance with the approved indications (effectiveness ∙ effect, administration∙ and dosage, precautions for use, etc.) in real-world clinical settings.

Regardless of whether they are currently undergoing pharmacotherapy for diabetes, all eligible patients who are considered suitable for Envlo Tab./Envlomet SR Tab. can be enrolled in this study. However, despite the decision to administer Envlo Tab./Envlomet SR Tab., observation is only possible with the subject's voluntary consent to participate in the study as determined by the investigator's medical judgment.

This observational study will collect demographic information, physical measurement, vital signs, and other relevant information up to 24 weeks after the administration of Envlo Tab./Envlomet SR Tab. in real-world clinical settings, irrespective of whether the medication is administered or not. Data will be collected based on medical records documented in real-world clinical settings. There are no mandatory visits, tests, or treatments specifically required by this observational study.

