### Efficacy Analysis Set

Subjects who meet the inclusion/exclusion criteria, have been enrolled in this study, received the investigational product at least once, and have had their weight measured post-baseline will be included in the efficacy analysis set.

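### The secondary therapeutic-response composite counts subjects already below 7% HbA1c at entry as responders even if they do not improve

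*Protocol*

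**What the plan says.** Section 8.1 (Endpoints) lists a proportion achieving therapeutic response among the secondary efficacy endpoints. The rule joins two limbs by OR, the first being baseline HbA1c minus visit HbA1c: "HbA1c at each evaluation time point) > 0.5% or HbA1c < 7%] at 12 and 24 weeks compared to baseline". Section 2.2 (Secondary Objectives) and the synopsis state the same rule.

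Entry is not tied to HbA1c:

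- Section 3.3 (Inclusion Criteria) takes patients with type 2 diabetes who "are about to receive Envlo Tab. or Envlomet SR Tab. for the first time". Its numerical threshold apart from age is BMI: "Patients with pre-obesity or higher stages according to the 2022 Obesity Treatment Guidelines of the Korean Endocrine Society".
- Section 3.4 (Exclusion Criteria) covers other diabetes types, contraindications, recent weight treatment, mental incapacity, pregnancy or breast-feeding, other studies and investigator judgement. None of these refers to HbA1c.
- Section 4.1 (Overall Design) admits treated and untreated patients alike: "Regardless of whether they are currently undergoing pharmacotherapy for diabetes, all eligible patients" judged suitable for the drug can join.

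The efficacy analysis set in Section 8.2 has no HbA1c condition either. Beyond eligibility and enrollment, it asks that subjects "received the investigational product at least once, and have had their weight measured post-baseline will be included in the efficacy analysis set".

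For the analysis, Section 8.2 plans descriptive statistics for each secondary variable at baseline, 12 and 24 weeks, with categorical variables as counts and percentages. Change is to be tested by a paired t-test or a Wilcoxon signed rank test.

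**The concern.** A measure named therapeutic response should credit a response. Here the second limb can be met on entry and simply kept. Subjects already below 7% count as responders whether they improve, stay the same or worsen, provided they remain below 7%. A subject who improves from 7.4% to 7.0% does not count.

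The study is single-arm (Section 3.2). In a controlled trial the comparator group would show how much of the rate comes from control already present at entry; here nothing in the endpoint does. The composite also has no usable baseline value: the change limb is zero by construction at baseline, so no before-and-after comparison of the composite can take these subjects out. The rate therefore mixes what happened on treatment with how well controlled the subjects were at the start.

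**Working it through.** **Plan's own figure.** The protocol states no expected response rate, so there is none to reproduce. Its one computed figure, about 210 subjects for weight change (Section 3.2), reproduces: d = 2.5/10.0 = 0.25, two-sided 5%, power 0.95, paired t-test gives n = 210 (power 0.950). It does not use HbA1c, so it is untouched by this point.

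**Step 1: apply the rule as written.**

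| Baseline | Visit | Fall | Fall > 0.5? | Visit < 7%? | Responder? |
|---|---|---|---|---|---|
| 6.5% | 6.5% | 0.0 | no | yes | yes |
| 6.2% | 6.9% | −0.7 (worse) | no | yes | yes |
| 7.4% | 7.0% | 0.4 | no | no | no |

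For anyone below 7% at baseline the first limb adds nothing, since a fall of more than 0.5 also leaves the value below 7%. For these subjects, response means only remaining below 7%.

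**Step 2: write the rate.** Let q be the share with baseline below 7%, s the fraction of those who are below 7% at the visit, and t the response rate among subjects at 7.0% or more.

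All-subject rate = q·s + (1 − q)·t

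All-subject rate − t = q·(s − t)

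- No change in anyone: s = 1 and t = 0, so the rate equals q. The rate restricted to baseline 7.0% or more is 0.
- Nobody enters below 7%: q = 0, and the two rates are the same.

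The documents give none of q, s or t.

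**Step 3: no drug effect, with random variation between visits.** All inputs here are assumptions: normal baseline HbA1c, and follow-up equal to baseline plus random variation with mean 0 and SD 0.3.

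| Assumed baseline mean (SD) | q | s | Restricted rate t | All-subject rate | Responders whose HbA1c rose, of all subjects |
|---|---|---|---|---|---|
| 8.0 (1.0) | 15.9% | 85.1% | 7.8% | 20.0% | 5.6% |
| 7.5 (1.0) | 30.9% | 87.9% | 9.7% | 33.8% | 11.7% |
| 7.0 (0.8) | 49.9% | 88.5% | 13.5% | 50.9% | 19.2% |

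Check of the middle row: 0.309 × 0.879 + 0.691 × 0.097 = 0.272 + 0.067 = 0.339, which agrees with 33.8% up to rounding of the inputs.

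In each scenario restriction removes most of the built-in rate but not all of it: 8% to 14% remains from chance movement across the thresholds. The simulation puts no error into the baseline value, so regression to the mean proper is not quantified here.

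**The case against.** Several points on the other side stand.

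- **The simple threshold endpoints are largely covered.** A reader might infer that "Proportion of subjects achieving HbA1c < 7% at 12 and 24 weeks compared to baseline", and its 6.5% counterpart, are equally defective. The documents do not support that: Section 8.2 plans descriptive statistics at baseline as well as at both visits, so the proportion already at goal will stand beside the follow-up proportion. Restricting those two is optional. The baseline proportion below 7% also hints at the composite's floor, though it is not a baseline value of the composite.
- **HbA1c change is its own secondary endpoint.** Average worsening would show there, which limits the harm.
- **The approved indication is improvement of glycemic control** (Sections 1.2 and 5). This makes entrants already at goal less likely. It states no threshold, however, and the study's stated interest is weight loss, so it does not exclude them.
- **The SAP, not shown, might restrict the denominator.** That is possible, but the responder rule is fixed in the protocol and the stated efficacy set carries no such restriction. The reference to baseline in the endpoint's wording does not restrict it either.
- **Maintained control can be a fair goal** for someone switched from another drug. This is a reason to keep the all-subject rate as supportive, not to call it a response without qualification.

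Two further inferences are tempting and should not be drawn. One is a specific percentage by which this trial's rate will be inflated; no baseline HbA1c distribution is given, so any such figure is an assumption. The other is that the endpoint spoils a comparison between sites; no such comparison is planned.

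**Conclusion.** The point holds for the therapeutic-response composite. Followed exactly, the protocol counts unchanged or worsened subjects as responders whenever they start and remain below 7%, and nothing in the entry criteria or the efficacy set keeps such subjects out. With no HbA1c change in anyone, the rate equals the share entering below 7%.

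The size is unknown, because it depends on that share, and the inflation is nil if the share is zero. The tabulated no-effect rates of 20% to 51% show only how the rule behaves under assumed distributions; they do not predict this study's result.

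The matter concerns one secondary endpoint. The primary weight/BMI analysis and the sample size are unaffected, and no decision rule uses the response rate. It is worth correcting because the correction is cheap and, with no control group, a reader of the published rate cannot separate response from prior control.

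**What to change.** In Section 8.1 and the synopsis, define therapeutic response among subjects with a baseline HbA1c of 7.0% or more, and repeat this in Section 2.2 so that the three statements agree. Show the all-subject rate as supportive, next to the baseline proportion below 7%. No change to enrollment or data collection is needed: HbA1c is on the Visit 1 list in Section 4.3, and Section 4.4 lets a result from the preceding 4 weeks stand in.

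The costs are a smaller denominator, a wider interval and a lower reported rate. Some regression to the mean remains, because the subset is selected on its baseline value, so the restricted rate is still not a pure drug effect. Laboratory values come from routine care, so some baselines may be missing. Those subjects would fall outside the restricted denominator, and their number should be reported; under the present rule they could be counted through the below-7% limb with no baseline at all.
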